# Conservative versus tailored surgical treatment in patients with first time lateral patella dislocation: a randomized-controlled trial

**DOI:** 10.1186/s13018-021-02513-3

**Published:** 2021-06-13

**Keywords:** Patella, Instability, Dislocation, Conservative treatment, Tailored surgical treatment

## Abstract

**Background:**

Patellar instability has a high incidence and occurs particularly in young and female patients. If the patella dislocates for the first time, treatment is usually conservative. However, this cautious approach carries the risk of recurrence and of secondary pathologies such as osteochondral fractures. Moreover, there is also risk of continuous symptoms apparent, as recurrent patella dislocation is related to patellofemoral osteoarthritis as well. An initial surgical treatment could possibly avoid these consequences of recurrent patella dislocation.

**Methods:**

A prospective, randomized-controlled trial design is applied. Patients with unilateral first-time patella dislocation will be considered for participation. Study participants will be randomized to either conservative treatment or to a tailored patella stabilizing treatment. In the conservative group, patients will use a knee brace and will be prescribed outpatient physical therapy. The surgical treatment will be performed in a tailored manner, addressing the pathologic anatomy that predisposes to patella dislocation.

The Banff Patellofemoral Instability-Instrument 2.0, recurrence rate, apprehension test, joint degeneration, and the Patella Instability Severity Score will serve as outcome parameters. The main analysis will focus on the difference in change of the scores between the two groups within a 2-year follow-up.

Statistical analysis will use linear mixed models. Power analysis was done for the comparison of the two study arms at 2-year follow-up with regard to the BPII Score. A sample size of N = 64 per study arm (128 overall) provides 80% power (alpha = 0.05, two-tailed) to detect a difference of 0.5 standard deviations in a t-test for independent samples.

**Discussion:**

Although several studies have already dealt with this issue, there is still no consensus on the ideal treatment concept for primary patellar dislocation. Moreover, most of these studies show a unified surgical group, which means that all patients were treated with the same surgical procedure. This is regarded as a major limitation as surgical treatment of patella dislocation should depend on the patient’s anatomic pathologies leading to patellar instability. To our knowledge, this is the first study investigating whether patients with primary patella dislocation are better treated conservatively or operatively with tailored surgery to stabilize the patella.

**Trial registration:**

The study will be prospectively registered in the publicly accessible database www.ClinicalTrials.gov.

## Introduction

Instability of the patella has a high incidence, particularly in the young and female population. Because the vast majority of unstable patella are unstable towards *lateral* and because instability is objective when the patella is fully *dislocated* the term “lateral patella dislocation (LPD)” is used throughout this study protocol.

*First time* or *primary* LPD is often treated conservatively. Although this is a cautious approach, it bears risks of recurrence and secondary pathologies like osteochondral fractures or patellofemoral osteoarthritis [1, 2]. Therefore, it might well be speculated whether primary LPD should better be treated surgically, not only for short time clinical improvement, but also for prevention of PF osteoarthritis. With this regard, several researchers already dealt with that issue. Table 1 gives an overview on current evidence on conservative vs. surgical treatment of patients with first-time lateral patella dislocation. However, only studies with level of evidence 1 or 2 were taken into account.

**Table 1 Tab1:** Current evidence on conservative vs. surgical treatment on patients with first-time lateral patella dislocation. Only studies with Level of Evidence 1 or 2 were taken into account

Author	Year	Randomization	Evidence Level	Surgical Procedure	Outcome Parameters	N	Mean Follow-Up Time	Findings	Misc
Apostolovic [3]	2011	no	2	loose body removal/refixation, medial capsular repair, lateral retinacular release	Cincinnati Score, recurrence rate	37	6 years	no difference	
Christiansen [4]	2008	yes	1	MPFL repair	recurrence rate, Kujala Score, KOOS Score	80	2 years	no difference	
Bitar [5]	2012	yes	1	MPFL reconstruction	recurrence rate, Kujala Score	41	44 months	surgery significantly superior in all parameters	
Camanho [6]	2009	yes	2	MPFL repair	recurrence rate, Kujala Score	33	3 years	surgery superior in all parameters	only “statistical trends”
Sillanpää [7]	2008	no	2	MPFL repair	recurrence rate, “return to sports”, Kujala Score	61	7 years	surgery superior in “return to sports”, rest: no difference	
Sillanpää [8]	2009	yes	1	medial repair or Roux-Goldthwait procedure	recurrence rate, “return to sports”, Kujala Score	40	7 years	surgery superior in recurrence rate, rest: no difference	
Petri [9]	2013	yes	1	MPFL repair	recurrence rate, Kujala Score, patient satisfaction	20	2 years	no difference	power 25%

Apostolovic et al. performed a prospective, non-randomized-controlled trial comparing 23 conservatively treated patients with 14 surgically treated patients in the context of primary LPD [3]. The criterion to treat surgically was the presence of (osteo)chondral lesions. Besides loose body removal/refixation, the patients received medial capsular repair and lateral retinacular release. The authors reported no differences between groups regarding recurrence rate or Cincinnati Knee scores, which goes along with the findings of Christiansen et al. [4]. Eighty patients with primary LPD were randomized to either conservative therapy or medial patellofemoral ligament (MPFL) repair. Patients were followed 2 years and demonstrated no significant differences between groups with regard to recurrence rate, KOOS Score, and Kujala Score.

However, there are considerable studies describing benefits of an initial surgical procedure. Bitar et al. conducted a randomized-controlled trial on primary LPD [5]. Thirty-nine patients were randomized to either non-operative treatment (immobilization and physical therapy) or reconstruction of the MPFL. At 2-year follow-up, the MPFL group was superior in terms of Kujala scores and recurrence rates. Camanho et al. also investigated patients with primary LPD [6]. Thirty-three patients were randomly assigned to either conservative treatment (immobilization and physiotherapy) or MPFL repair. The authors reported superior results in the surgical group. Two studies very similar to each other were published by Sillanpää et al. in 2008 and 2009 [7, 8]. The outcome parameters recurrence rates, Kujala scores and “return to sports – rate” were determined in patients with conservative treatment and in those with surgery. While the surgical group was superior in terms of “return-to-sports” there were no significant differences in the other outcome parameters [7]. In contrast, Sillanpää et al. stated in the following randomized-controlled study that patients treated surgically were superior in terms of recurrence rate but not in the other parameters [8]. Finally, a randomized-controlled trial published by Petri et al. should be mentioned [9]. In a multicentric approach, patients with primary LPD were randomized to either conservative treatment or MPFL repair. Unfortunately, the trial was discontinued after 20 patients and did therefore not reach sufficient power.

In synopsis of the abovementioned studies, there is no consensus on whether patients with first time LPD should be treated conservatively or surgically (Table 1). Besides, in most of those studies the surgically group was uniform, meaning that all patients were treated with the same surgical procedure. In addition, previous studies have focused more on the rate of re-dislocation and were not based upon modern and relevant PROM scores. Treatment with the same surgical procedure is regarded as a major limitation as surgical treatment of LPD should be done in a tailored manner, depending on the patient’s anatomic pathologies which lead to LPD [10, 11]:

### MPFL reconstruction

Reconstruction of the medial patellofemoral ligament (MPFL) is a proven technique for LPD [10–12] and today’s established standard treatment. However, some authors have reported a considerable complication rate [13, 14]. Many failures were reported due to inappropriate indications. The latter means performing *isolated* MPFL in patients with coexisting severe osseous pathologies like high-grade trochlear dysplasia or a pathologic tuberositas-tibiae-trochlea-groove distance (TT-TG distance) [15, 16]. Isolated MPFL reconstruction is regarded as inappropriate in patients with: (1) TT-TG distance > 20 mm, (2) femoral anteversion ≥ 40° (n. Waidelich/Strecker), (3) high-grade trochlea dysplasia, (4) severe patella alta, and (5) tibiofemoral valgus > 5°. Moreover, it is striking that most abovementioned studies applied MPFL repair. Only Bitar et al. performed MPFL reconstruction [5]. With accurate indications and surgical technique isolated MPFL reconstruction provides a good outcome in patients with LPD [17, 18].

### Trochleoplasty

When the trochlea is flat or convex (dysplasia Dejour type B, C or D) a “deepening trochleoplasty” should be considered. The aim of the trochleoplasty is to (a) reduce the too prominent anterior bone stock, (b) create better conformity with the patella (concave groove) and a lateral trochlea facet as restraint against the lateralizing quadriceps pull, and (c) to lateralize the groove when there is trochlea asymmetry in order to normalize TT-TG distance [19, 20]. Many authors have reported that trochleoplasty leads to a good clinical outcome in patients’ LPD due to a dysplastic femoral trochlea [12, 19, 21–27].

### Tibial tuberosity transfer

The most popular type of osteotomy in the setting of LPD is certainly the osteotomy and transfer of the tibial tuberosity (TTT). Many articles reported good clinical success for medialising TTT in patients with LPD and high TT-TG values [12, 28–32]. Similarly, good results were found for distalizing TTT in patients with LPD and patella alta [33, 34]. TTT can be tailored to the pathology of the patient by performing combined medialization and distalization.

### Derotational osteotomy

Derotational osteotomies of the femur (externally rotating) provide good results in patients with LPD and associated torsional deformities [35–37]. However, the literature is incongruent on whether rotational osteotomies of the femur should be performed at the proximal or distal aspect [38–41]. In the authors hand’s, derotational osteotomy is carried out at the distal femur.

### Varus osteotomy

Distal femoral varus osteotomies have been described in the recent years to be successful in the management of patellofemoral instability with genu valgum [42]. They have been described as promising and useful in the management of patellofemoral instability with genu valgum, leading to an improved patellar alignment and to a reduction in the risk of recurrent patella dislocation [42, 43].

### Aims of the study

Due to the abovementioned lack of consistent evidence, it is the aim of the study to investigate whether patients with primary LPD are better treated conservatively or operatively (tailored surgery to stabilize the patella).

### Hypotheses

It is hypothesized that patients with primary LPD when treated either conservatively or surgically (tailored stabilizing procedure) will show significant differences *after two years* in terms of the Banff Patellofemoral Instability-Instrument (BPII) 2.0 (hypothesis 1). We assume as well that the abovementioned groups also differ significantly in terms of recurrent patella dislocations (hypothesis 2).

## Methods

### Study design and participants

A prospective, randomized-controlled trial design is applied. Before commencement of the study, approval of the ethical committees (EC) of the participating centers is obtained. Patients with objective, unilateral first time LPD, based on patient’s history and physical examination, will be considered for participation. After written informed consent the patients are included in the study at their first visit at the emergency department. Excluded are (a) patients with osteochondral lesions requiring removal/refixation, (b) patients with recurrent LPD, (c) pregnant patients, and (d) patients > 45 years of age and patients with physical maturity Kramer stage 1 to stage 3a [44, 45].

Clinical workup includes thorough history, physical evaluation, plain radiographs, and magnetic resonance imaging (MRI) in all patients. When the physical examination reveals suspicion of maltorsion syndrome, MRI (or CT scan) is done of the hip, knee, and ankle to quantify femoral and tibial torsion. When the physical examination reveals suspicion of a relevant genu valgum or varum a long-standing x-ray is performed.

### Randomization

Patients successfully included in the study are then randomized to either conservative treatment or to a tailored patella stabilizing treatment. Block randomization will be used to ensure a balanced ratio of group sizes. The total number of patients will be divided into blocks of the same size. This will be followed by a balanced but random allocation of the treatment groups in the individual blocks. Patients will be divided into 10 blocks of 16 patients each and will be assigned to the two different treatment groups.

Block randomization is performed in advance with SPSS (IBM SPSS statistics, Chicago, IL, USA) to guarantee equal group sizes. Syntax and seed for the random number generator are kept for reproducibility of the processes.

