### Dropouts and exclusion of the clinical trial

To account for 20% attrition during the study period (“dropouts”), it is planned to recruit 80 patients per study group (160 overall) at baseline (see section “Statistics”). If patients request *after* randomization on their own free will a different treatment method — for example, if a patient requests surgery in conservative group — they have to be excluded from the study.

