### MPFL reconstruction

#### MPFL reconstruction is applied in all patients of the surgical group

MPFL reconstructionhas been reported with a high variety of surgical techniques (graft type, single vs. double bundle, type of fixation, etc.). The specific surgical technique is carried out on surgeon’s preference at the respective center of the multicentric study.

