### Statistics

Patient characteristics will be presented as means, standard deviations, and percentages. The main analysis will use linear mixed models that allow data modeling with a varying number of assessments per patient and time-varying covariates. Such a model will be used to compare the differences in changes over time between the two study groups. The following terms will be included in the model: a random baseline, a first-order autocorrelation covariance matrix, a fixed-effect patient group, a fixed effect time point, and the group-by-time interaction (reflecting the intervention effect). The BPII 2.0 will serve as the primary outcome parameters. The main analysis is “intention to treat” and will focus on the group difference in the change of BPII 2.0 scores between pre-op and 2-year follow-up. The abovementioned secondary outcome parameters will be analyzed with the same model.

Power/sample size analysis was done for the comparison of the two study arms at a 2-year follow-up with regard to the BPII Score. As there are no specific minimal important difference (MID) for the BPII available from the literature, we defined the MID to be 0.5 standard deviations following general recommendations from the literature [58]. A sample size of N = 64 per study arm (128 overall) provides 80% power (alpha = 0.05, two-tailed) to detect a difference of 0.5 standard deviations in a t-test for independent samples. To account for 20% attrition during the study period (“dropouts”), we plan to recruit 80 patients per study group (160 overall) at baseline.

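### One published, constant block size of 16 lets a recruiter who can follow the whole sequence deduce the end of each block: about 18 of 160 allocations on average at most, near zero under other arrangements

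*Protocol article*

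**What the plan says.** The Randomization section sets a single block length: "The total number of patients will be divided into blocks of the same size". It requires balance within each block, "This will be followed by a balanced but random allocation of the treatment groups in the individual blocks", and then gives the number and length: "Patients will be divided into 10 blocks of 16 patients each and will be assigned to the two different treatment groups". The list is drawn up before recruitment: "Block randomization is performed in advance with SPSS (IBM SPSS statistics, Chicago, IL, USA) to guarantee equal group sizes". The total agrees with the recruitment target under Dropouts and exclusion of the clinical trial, where "it is planned to recruit 80 patients per study group (160 overall) at baseline".

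The interventions are a motion-restricting brace with physical therapy in one arm and patellar surgery in the other. The article describes no masking and does not use the term open-label, but treating staff cannot be unaware of which of these a patient received.

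More than one site takes part. The surgical methods refer to the technique used "at the respective center of the multicentric study". The Randomization section does not say whether blocks are kept within a centre or drawn from one list for all centres.

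**The concern.** When a block is known to hold 8 allocations to each arm, its tail is fixed as soon as one arm has used its 8 places. The last allocation of every block is always fixed, and sometimes several before it. Because the length is constant and public, anyone who follows the sequence can count to these points.

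Foreknowledge of the next allocation matters most when the arms are as different as surgery and a brace. A recruiter who knows what comes next can, knowingly or not, delay, encourage or discourage a particular patient. The arms then differ in who was enrolled, and later adjustment cannot be relied on to remove this. The primary outcome, BPII 2.0, is self-reported, so a difference in the kind of patient enrolled could carry into it.

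**Working it through.** **The plan's own figure.** The Statistics section says that 64 per arm "provides 80% power (alpha = 0.05, two-tailed) to detect a difference of 0.5 standard deviations in a t-test for independent samples". The exact two-sample t-test calculation gives 63.8, rounded up to 64, with power 80.1%. "To account for 20% attrition during the study period", 64 / (1 − 0.20) = 80 per arm, 160 in total. Ten blocks of 16 also make 160. The figures agree, and nothing below changes them.

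**Inputs.** Block length 2m = 16, so m = 8 per arm; 10 blocks; 1:1 allocation within blocks (Randomization section). The number of centres and whether blocks are kept within a centre are not given, so both are treated as assumptions.

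**Step 1: deducible allocations for an observer who sees everything.** In a randomly permuted block of 2m, the probability that the last k allocations are all to the same arm is 2·C(2m − k, m) / C(2m, m). Summing over k = 1 to m gives the expected length of the determined tail:

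E = 2m / (m + 1) = 16 / 9 = 1.78 per block.

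The first terms for m = 8 are 1.000 (k = 1), 0.467 (k = 2), 0.200 (k = 3) and 0.077 (k = 4). Over 10 blocks, 10 × 16/9 = 17.8, and 17.8 / 160 = 11.1%. Simulated lists give a mean of 17.8, a 95% range of 12 to 25, and a floor of 10 (one per block).

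**Step 2: how the number depends on what recruiters see.**

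| Assumption | Expected deducible allocations of 160 |
|---|---|
| Single centre, or whole blocks within a centre, or allocations shared between centres | about 18 |
| One list, 2 equally recruiting centres, each sees only its own patients | below 0.1 |
| One list, 3 or 4 such centres | about 0 |

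The second and third rows were simulated by assigning each place in a block to a centre at random. An allocation counted as deducible only if that centre had already seen 8 of one arm in the block.

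**Step 3: is 16 the wrong number?** No. By the same formula, a fixed block of 8 gives 20 × 8/5 = 32 deducible allocations, and a fixed block of 4 gives 40 × 4/3 = 53. The weakness is that the length is constant and disclosed.

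**Step 4: what varied lengths change.** Take three blocks of 12, four of 16 and three of 20 in random order: 36 + 64 + 60 = 160, and each block is balanced, so 80/80 is kept.

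- Certainty from the known total: once one arm reaches 80, the rest are fixed. This is the tail of the last block, on average (3 × 12/7 + 4 × 16/9 + 3 × 20/11) / 10 = 1.77, so about 2.
- Worst case: a recruiter who tracks everything and also knows the exact set of lengths, but not their order, can still deduce about 4 on average.
- Guessing: always predicting the arm with fewer allocations so far is right 62.8% of the time with fixed blocks of 16 and 62.7% with hidden 12/16/20. In both cases this is about 100 of 160, against 80 by chance. Hidden blocks of 4, 6 and 8 would raise it to about 68%, so the blocks should not be made shorter.

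**The case against.** The strongest reply is that the exposure may not exist. The Randomization section reads naturally as one set of 10 blocks for the whole trial and mentions no strata by centre. If several centres draw on that list and each knows only its own patients, almost nothing can be deduced. A reader might infer from the block size alone that about 18 allocations are certain whatever the set-up. The document does not support that. The figure is an average, and it requires a recruiter to see every earlier allocation in the block and to know where the block starts.

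Three further points stand.

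- Sixteen is already a defensible length, less predictable than shorter fixed blocks.
- A recruiter who simply guesses the under-represented arm does as well under the proposed scheme as under the present one. The change removes certainty, not guessing.
- Consent and inclusion take place at the first emergency visit, and only patients already included are randomized. This limits, though it does not remove, the scope for timing entry.

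It would also be wrong to infer that site staff hold the list. The article says that the syntax and seed are kept for reproducibility, not by whom. Custody and concealment of the list are details that a condensed article may leave to the full protocol, so their absence is no fault here.

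The reply does not dispose of the point. The constant length is a rule that the article states and makes public, not a missing detail. The arrangement that makes it matter, blocks within a centre, is a common one that the text does not exclude.

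**Conclusion.** The point holds in a limited form. Publishing one fixed block size in a trial whose treatments cannot be masked from staff is a minor, avoidable weakness. The expected number of deducible allocations runs from about 0 to about 18 of 160 (0 to 11%). The upper figure assumes that recruiters can follow all allocations in a block and know the block starts; the lower assumes a shared list with local knowledge only. The article does not settle which is closer.

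There is no contradiction and no wrong figure. The document does not show that any recruiter can see the sequence or that bias will occur.

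**What to change.** In the Randomization section, replace the statement of 10 equal blocks of 16 by one saying that block sizes vary at random and are not disclosed to recruiting staff until recruitment closes. Lengths of 12, 16 and 20 in random order, summing to 160, would do; the actual lengths should not be published while recruitment is open. One sentence saying whether blocks run within a centre would let a reader judge which end of the range applies.

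The cost is a few lines of SPSS syntax before the list is issued. If recruitment stops in mid-block, the largest possible imbalance rises from 8 (half of 16) to 10 (half of 20). If a list of fixed blocks is already in use, the places not yet issued could be regenerated in the same way.
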